**Figure 2 f2:**
[figure not shown]
Study schedule for the participants in this randomized, double-blind, controlled trial. AE, Aerobic Exercise; fNIRS, Functional Near-Infrared Spectroscopy; HD-tDCS, High-definition transcranial direct current stimulation; MRI, magnetic resonance imaging.

### Data monitoring

Despite being deemed low-risk for participants, the Institutional Review Board of the Second Affiliated Hospital of Xinxiang Medical University opted to form a data monitoring committee for the ensuing experiments to safeguard data quality and participant well-being.

### Harms

To evaluate the safety and potential adverse effects of HD-tDCS, this study will thoroughly investigate both severe and mild adverse events. All participants will be required to complete the HD-tDCS Adverse Reaction Scale (ARS), which encompasses common side effects such as tingling, mild redness, itching, and discomfort at the stimulation site. Participants will rate their adverse reactions on a scale from 0 to 5, with all occurrences documented in the CRFs. The HD-tDCS equipment will be operated by trained therapists proficient in its use, aiming to minimize the risk of participants encountering any significant health hazards or adverse effects. In the event of a severe adverse reaction, the participant will be withdrawn from the study, and the incident will be promptly reported to the ethics committee.

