## Methods

### Study design

This randomized, double-blind, controlled clinical trial evaluates the efficacy of combining HD-tDCS with AE to improve cognitive function in individuals with CIAS. Eligible participants will be randomly assigned to one of four groups in equal proportions (1:1:1:1): MRI-guided HD-tDCS +AE (Group 1), MRI-guided HD-tDCS alone (Group 2), AE alone (Group 3), and a control group (Group 4). Assessments will be conducted at baseline (T0), at 2 weeks (T1), at 4 weeks (T2), and at 6 months post-intervention (T3). The specific intervention measures for each group are delineated as follows: the MRI-guided HD-tDCS + AE group first undertakes a 15-minute warm-up exercise. Subsequently, HD-tDCS and AE treatments are administered concurrently for a duration of 30 minutes. The HD-tDCS group receives 30 minutes of electrical stimulation per session. The AE group’s intervention comprises a 15-minute warm-up followed by a 30-minute formal AE stage, amounting to a total of 45 minutes. The control group does not receive HD-tDCS or AE but instead is provided with routine psychiatric care, including regular psychiatric follow-ups, medication management, and general health guidance, but no experimental interventions. Each intervention for the aforementioned groups is conducted once daily, five days a week, over a period of four weeks, culminating in a total of 20 sessions. The study design is illustrated in **Figure 1**.

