### Statistical methods

The Shapiro-Wilk test will be employed to determine whether the quantitative data conform to a normal distribution. When the quantitative data are normally distributed, they will be described using the mean and standard deviation. If the data deviate from a normal distribution, the median and interquartile range will be utilized for presentation. Categorical data will be presented as counts and percentages. To evaluate differences in baseline characteristics among groups, appropriate statistical tests such as t-tests, nonparametric tests, chi-square tests, Mann-Whitney U tests, or ANOVA will be selected based on the type and distribution of the data. Additionally, Fisher’s exact test or chi-square test will be used to compare adverse reactions between groups.

This study will adhere to the CONSORT guidelines and perform data analysis based on the intention-to-treat principle, ensuring that all participants are evaluated according to their initial randomization assignments. To assess differences in primary and secondary outcomes both between and within groups over time, generalized linear mixed models and repeated-measures ANOVA will be employed as appropriate. A stepwise model selection approach will be implemented to derive a succinct multivariate regression model. Age, gender, and the Defined Daily Dose (DDD) of antipsychotic medications will be included as covariates in all models. The treatment effect will be evaluated using the likelihood ratio test to ascertain whether the coefficients for treatment and the interaction between time and treatment are both zero. To correct for multiple comparisons across time points, the Bonferroni correction method will be applied to adjust the p-values. All statistical analyses will be conducted using SPSS version 20.0, with a significance threshold set at *P* < 0.05 to denote statistical significance. Research framework is illustrated in **Figure 2**.

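### The only scheduled safety instrument is a stimulation-effects scale given to all four arms: it fixes the direction of the site-reaction comparison in advance and does not collect exercise-related events comparably.

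*Protocol article*

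**What the plan says.** The Harms section of the protocol article gives its purpose as "To evaluate the safety and potential adverse effects of HD-tDCS, this study will thoroughly investigate both severe and mild adverse events". Exercise is not mentioned there. One instrument is named: "All participants will be required to complete the HD-tDCS Adverse Reaction Scale (ARS". It is a scale "which encompasses common side effects such as tingling, mild redness, itching, and discomfort at the stimulation site". On scoring, the section says "Participants will rate their adverse reactions on a scale from 0 to 5, with all occurrences documented in the CRFs".

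Table 2 has a single row under Safety, the ARS, ticked at T1, T2 and T3.

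Statistical methods says "Fisher’s exact test or chi-square test will be used to compare adverse reactions between groups". It does not restrict the groups or name the data source.

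On exposure, Study design gives Group 3 exercise only, and for Group 4 it says "The control group does not receive HD-tDCS or AE". The limitations paragraph of the Discussion confirms that there is neither a sham stimulation nor a sham exercise condition. The end of the Background makes the feasibility and safety of the whole approach an aim.

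Three other statements bear on safety. The data management section sets up an independent committee that monitors adverse events. The Aerobic exercise section has heart rate recorded during training. It also has blood pressure taken before and after sessions.

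**The concern.** A scale written for one intervention is given to arms that do not receive it, and adverse reactions are then tested between arms. For reactions at the stimulation site, 24 of the 48 patients have no site to rate. A significant result on those items would mainly restate who wore electrodes.

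The other half of the combination is treated differently. Groups 1 and 3 exercise for 20 sessions, and Group 1 does so during stimulation. None of the named items is directed at exercise, and no other form is scheduled. The harms table could then show reactions concentrated in the stimulated arms and little in the exercise arm, partly because of what was asked. A reader who wants the safety of the combination would learn about its stimulation component and much less about its exercise component. A later analysis plan can choose a different test, but it cannot recover events that no scheduled form collected.

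**Working it through.** **Inputs.** Arm size: 48 / 4 = 12 (Sample size calculation). Stimulated arms: Groups 1 and 2. Unstimulated arms: Groups 3 and 4 (Study design). Test: Fisher's exact or chi-square (Statistical methods). Significance level: 0.05. The protocol gives no harms figure to reproduce, and the sample size itself is not in question here.

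**Assumptions.**
- The protocol gives no site-reaction rate, so a range for the true rate q in the stimulated arms is shown.
- Any score above 0 counts as a reaction.
- The rate in Groups 3 and 4 is 0 for site items.
- All 12 patients per arm are observed.

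**Step 1: what the scale can show.**

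| Group | Stimulation | Exercise | Can have a true stimulation-site reaction | Scheduled form aimed at exercise events |
|---|---|---|---|---|
| 1 | yes | yes | yes | none |
| 2 | yes | no | yes | not applicable |
| 3 | no | yes | no | none |
| 4 | no | no | no | not applicable |

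On site items, Groups 1 and 2 can only equal or exceed Groups 3 and 4. Group 1 versus Group 2 is the one pair in which both arms are exposed.

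**Step 2: one stimulated arm against one unstimulated arm.** For x of 12 against 0 of 12, the two-sided Fisher P is 2 × C(12,x) / C(24,x).
- x = 4: 2 × 495 / 10,626 = 0.093
- x = 5: 2 × 792 / 42,504 = 0.037
- x = 6: 2 × 924 / 134,596 = 0.014

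Five reactions among 12 stimulated patients are therefore enough for P < 0.05. The chance of at least five is the sum over j = 5 to 12 of C(12,j) q^j (1 − q)^(12 − j).

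**Step 3: all four arms together.** The counts are (i, j, 0, 0), with i and j binomial (12, q). For each pair, the exact P of the 4 × 2 table (Fisher-Freeman-Halton) was found by enumeration. The probabilities of pairs with P < 0.05 were then added.

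| Assumed rate q | Chance of P < 0.05, one stimulated v one unstimulated arm | Chance of P < 0.05, four-arm exact test |
|---|---|---|
| 10% | 0.004 | 0.051 |
| 20% | 0.073 | 0.369 |
| 30% | 0.276 | 0.757 |
| 40% | 0.562 | 0.949 |
| 50% | 0.806 | 0.995 |

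The direction is fixed throughout. Significance is not: it is unlikely at 10% and close to certain at 50%.

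**The case against.** The strongest reply is that the protocol promises more than one scale. The Harms section undertakes to investigate events of either severity and to document all occurrences, a committee monitors adverse events, and heart rate and blood pressure are recorded in the exercise arms. This is also an article, which need not reproduce its case report forms. That stands against one tempting reading, that exercise harms go unmeasured. The documents do not support it. What remains is narrower. The general undertaking is made in a sentence about HD-tDCS and names no form or schedule. A committee reviews what has been collected. The heart rate and blood pressure records are not in the Safety part of Table 2 and are not tied to the between-group test. The complaint is therefore about a stated choice, one device-specific scale for all arms, and not about an omitted form.

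A second reply is that the ARS items are given only as examples. The scale may hold items that are not tied to a site, and an unstimulated patient may report itching or tingling. Statistical methods also does not say that the ARS is the source for the test. This stands as a limit: the structural zero applies only to site items. That the ARS feeds the test is an inference, though a natural one, because both sections speak of adverse reactions and no other safety instrument is scheduled.

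A third reply is that an excess of site reactions under stimulation is a real harm, correctly attributed. That is right. The counts are worth reporting; it is the P value against unexposed arms that adds little.

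**Conclusion.** The point holds in limited form. The only scheduled safety instrument is specific to stimulation, all four arms complete it, and the between-group comparison is unrestricted. For stimulation-site items, the direction of any stimulated versus unstimulated comparison is known before the trial starts. Exercise-related events in Groups 1 and 3 are not systematically collected in a form comparable across arms.

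A reader might infer that the test result itself is settled beforehand. The figures do not support that. In the four-arm test, the chance of significance runs from about 5% at a 10% reaction rate to 76% at 30% and 99.5% at 50%, and the protocol gives no rate. Nor does the inference apply to Group 1 versus Group 2, which remains informative, or to any items not tied to a site.

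The conclusion rests on the ARS being the data source for the between-group test and on a zero rate of site reactions without stimulation. The primary cognitive outcome is not affected.

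**What to change.** 1. At T1, T2 and T3, use one common adverse-event form in all four arms: an open question plus a short checklist that includes exercise-related events. Add it as a row under Safety in Table 2 and name it in Harms.
2. In Statistical methods, base the between-arm Fisher or chi-square test on that form.
3. Compare the stimulation-site items of the ARS only between Groups 1 and 2, or report them descriptively.
4. Report events noted at treatment sessions separately and keep them out of the comparison with control. Groups 1 to 3 have 20 sessions and Group 4 has none, so counting session reports would give the active arms up to 20 more occasions on which an event could be recorded.

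The cost is one short extra form at visits that already take place, one row in Table 2, and small edits to Harms and Statistical methods. The change should come early, because events that were not asked about cannot be reliably recovered later.

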### Auditing

To ensure data quality, a dual verification system will be implemented throughout the study, covering both the treatment phase and the 6-month follow-up period. The lead researcher will conduct weekly evaluations of CRFs and estimation forms. Additionally, a bi-weekly comparison between hard copy and electronic records will be performed to verify consistency. Any discrepancies will be documented and discussed in team meetings to facilitate prompt corrective actions.

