### Blinding

All participants and researchers will remain blinded throughout the research process. During the entire research process, the designated stimulus conditions will be kept strictly confidential and will only be disclosed to the principal researcher. Four distinct groups will be tasked with administering the treatment, with strict measures in place to prevent inter-group communication regarding the particulars of each treatment. Each group will be informed only of its own treatment protocol and will remain unaware of the grouping details or the treatment plans of the other groups. The principal investigator will assign specific measures to each group, which will then implement the experimental treatment for their respective patient cohorts. Patients will remain unaware of their group allocation and will be instructed not to discuss the grouping, the treatment received, the completion of questionnaires, or any other aspects of the experimental protocol. During the phase of result measurement, personnel involved in data collection and analysis will also be blinded to the grouping information and specific measures. Subsequently, the principal investigator will conduct two unblinding procedures: the first will occur before data locking, and the second will follow data analysis. The initial unblinding will occur after data locking, organizing the data into groups 1–4 without disclosing the actual correspondence between these groups and their respective identities. The second unblinding will take place after the data analysis, explicitly revealing the specific identities of groups 1-4. Furthermore, to ensure that participants are unaware of their group assignments, the intervention activities will be conducted in designated rooms. Although the researchers will be aware of the group assignments, they must not disclose this information to the participants and will not be involved in the evaluation or analysis of the study. Additionally, the evaluators and data analysts will remain unaware of the intervention group’s situation throughout the entire research process.

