All researchers involved in data management and statistical analysis will remain blinded to the grouping information throughout the entire process. Specifically, data will be analyzed using coded group identifiers (e.g., Group A, B, and C), and the blinding code will remain undisclosed until the completion of the statistical analysis and the locking of the database. This procedure aligns with the principle of the blind method for minimizing assessment bias, as outlined in clinical trial protocols (46).

A Blinding Integrity (BI) assessment will be conducted following the final intervention session. Participants will be required to specify their perceived group allocation via a forced-choice questionnaire, asking: “Which intervention do you believe you received?” The response options will include (1): Combined HD-tDCS and AE (2), HD-tDCS alone (3), AE alone (4), Control, or (5) Unsure. To rigorously assess the blinding effect, Bang’s Blinding Index (BI) will be calculated for each group. This index allows for the distinction between genuine unblinding and random guessing. The BI is the primary tool for quantitatively evaluating the effectiveness of blinding implementation in clinical trials. By calculating the BI separately for each group, we can accurately assess the maintenance of blinding across different intervention groups (47).

Unlike drug trials, these trials—such as those involving surgery, rehabilitation, psychological, and physical therapy—cannot physically blind the “treatment itself” (48). During the informed consent process, we informed participants that the study was designed to investigate the effects of non-pharmacological interventions on cognitive function of individuals with schizophrenia. In the informed consent form, all intervention measures were described as “interventions with potential benefits,” without disclosing which group was the experimental group and which was the control group.The language used in the informed consent form was intentionally general to avoid revealing specific differences between groups, thereby minimizing the expectancy effect. Upon completion of the study, it is imperative to fully disclose the actual research design and the group assignments to all participants.

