### Date management

The evaluation of cognitive function and the severity of psychiatric symptoms will be conducted by two psychiatrists, who will remain blinded to the group assignments. All demographic information and scale-related data will be recorded in electronic Case Report Forms (eCRFs) and stored on a designated website. Access to the securely stored eCRFs will be restricted to the project leader and the principal investigator. To maintain confidentiality, anonymization will be implemented during data entry by substituting patients’ actual names with unique identification numbers. The independent data monitoring committee will be established to monitor safety, the occurrence of adverse events, and advise on trial design decisions.

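### The principal investigator knows the allocation and has eCRF access, so the statement that everyone in data management stays blinded cannot hold as written

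*Protocol article*

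**What the plan says.** Four parts of the protocol article bear on who knows the allocation and who handles the data.

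- **Blinding, on the key.** The article says that "the designated stimulus conditions will be kept strictly confidential and will only be disclosed to the principal researcher". It adds that "The principal investigator will assign specific measures to each group" and that "the principal investigator will conduct two unblinding procedures". The first of these procedures consists of "organizing the data into groups 1–4 without disclosing the actual correspondence between these groups and their respective identities"; the second reveals which treatment each group number stands for.
- **Blinding, on data handling.** "All researchers involved in data management and statistical analysis will remain blinded to the grouping information throughout the entire process".
- **Date management** (heading as printed). "Access to the securely stored eCRFs will be restricted to the project leader and the principal investigator". The same section has two blinded psychiatrists rate cognition and symptom severity.
- **Auditing.** "The lead researcher will conduct weekly evaluations of CRFs and estimation forms". This runs through treatment and the six-month follow-up. Paper and electronic records are compared every two weeks, and discrepancies are recorded and taken to team meetings.

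**The concern.** The statement on data management and analysis is absolute: it covers every researcher in those functions, for the whole process. The role assignments elsewhere put at least one person who knows the allocation inside data management.

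This matters more here than in a sham-controlled trial. The limitations paragraph of the Discussion concedes that there is neither sham stimulation nor sham exercise and that participant blinding is therefore incomplete. The Blinding section concedes that the researchers giving the interventions know the assignments. Blinded rating and blinded handling of the data are then the main protections left. If someone who knows the arms can see outcome records while the database is open, there is an unguarded route by which queries and corrections could depend on arm. With 12 patients per group, a few altered records could matter, particularly on the rater-scored secondary scales (PANSS, BPRS, SDSS).

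**Working it through.** No arithmetic decides this point. The check sets the statements side by side.

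1. **Does the principal investigator know the allocation?** Yes. This person decides which treatment each group receives, so the link from group to treatment is known. This person also conducts the step that sorts the data into groups 1–4, which requires the link from patient to group. Together the two links give each patient's treatment. If the principal researcher to whom the conditions are disclosed is the same person, the knowledge exists from the start. If not, it exists at the latest from the first unblinding step.

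2. **Does the principal investigator take part in data management?** Yes, in two ways. The data management section names this person as one of two with eCRF access, and the Blinding section has this person conduct the sorting of the data by group.

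3. **Is the blinding statement compatible with 1 and 2?** No. It admits no exception by person or by time. One person who both handles the data and knows the allocation is enough to contradict it.

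4. **Is the database closed when the data are sorted?** The article gives both answers. The Blinding section places the first unblinding before data locking in one sentence and after it in the next. On the former reading, the principal investigator sorts data by arm while records can still be changed.

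5. **Does the weekly review add exposure?** Only conditionally. Auditing names the *lead researcher*. The article also uses *principal researcher*, *principal investigator* and *project leader*, and defines none of the four. If the lead researcher is the principal investigator, an unblinded person reviews case report forms and rating forms during the trial. If the lead researcher is the project leader, who is nowhere said to hold the key, this part falls away. Steps 1 to 3 do not depend on it.

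6. **How much outcome data would the review touch?** Weekly review over 4 treatment weeks and about 26 follow-up weeks gives 4 + 26 = about 30 review occasions. Table 2 schedules outcome assessments at only four visits (T0, T1, T2, T3), three of them after baseline and none between T2 and T3. Most review occasions would therefore bring no new outcome form.

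**The case against.** The strongest reply is that the protections that matter most are stated and that nothing here contradicts them. Two blinded psychiatrists do the ratings, evaluators and analysts stay unaware throughout, staff who give the interventions take no part in evaluation or analysis, the analysis uses coded groups, and names are replaced by numbers at data entry. The primary outcome is a battery of 10 cognitive tests. All of that stands, and it confines the point to data handling.

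It can also be said that the eCRF restriction is a confidentiality rule, that access is not the same as managing data, and that read and write permissions belong in a fuller document. This has some force on access alone. It does not cover the sorting of data by group, which is data handling by any reading, and it does not rescue a claim that the article makes without exception.

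Several stronger readings are tempting, and the article does not support them:

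- *That the principal investigator alone holds the key.* The sentence on disclosure suggests it, but the Randomization section has an independent researcher generate the allocation, and the treating researchers know the assignments.
- *That the weekly reviewer is the unblinded person.* This is possible but not stated. The data management section lists the project leader and the principal investigator separately, so the lead researcher could be either.
- *That this person settles discrepancies or may change ratings.* Auditing says that discrepancies are discussed by the team, directly after describing a comparison of paper with electronic records. No sentence gives any one person authority to alter a score.
- *That every outcome form is exposed about 30 times.* That counts calendar weeks, not outcome assessments.

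**Conclusion.** The contradiction is real and rests on the Blinding and data management sections alone: the principal investigator knows the allocation, has eCRF access and conducts the sorting of data by group, while everyone in data management is said to be blinded throughout. As written, the trial claims a safeguard that its role assignments do not provide.

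The size of any consequence cannot be derived from the article. The defect lies in data handling. It does not reach the stated blinding of raters and analysts, and no bias is shown, only a route that is left open. The conclusion assumes that *principal investigator* means the same person wherever it appears. It does not need *lead researcher* to be that person; if it is, the exposure is larger, because it then includes regular review of outcome forms during the trial.

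The point deserves action before data accumulate, because blinding lost during the trial cannot be restored afterwards.

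**What to change.** 1. Define the four role titles and state for each whether the holder knows the allocation.
2. Give eCRF access before lock, the weekly form review, the resolution of discrepancies and the sorting of data by group code to an existing team member who does not hold the key. The project leader would serve, if kept blinded.
3. Withhold the principal investigator's access to outcome data until the database is locked, and state once, unambiguously, whether the first unblinding step comes before or after lock.
4. If the roles cannot be separated, narrow the blinding statement to outcome assessors and analysts, and report that data handling was not blinded.

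The first three items reassign existing roles and clarify text. The cost is that the principal investigator loses direct oversight of outcome data before lock. That is a small loss, since the article already provides for an independent data monitoring committee to watch safety and adverse events. The fourth item costs only wording, but it leaves the route to bias open.
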